## Packaging and Labeling of Study drug

Amphomul^®^ will be packed in a carton labeled with at least the following information according to GMP guideline Volume 4, Annex 13 and the local law: protocol number, drug name, route of administration, storage, lot no., expiry date, “STRICTLY FOR CLINICAL TRIAL USE ONLY”.

The outer big white carton, in turn, will contain small manufacturer-provided boxes containing glass vials of Amphomul^®^*.*

##### Original label for Amphomul^®^ vial

Each vial of Amphomul^®^, in addition to its original print provided by the manufacturer/ Sponsor bearing the manufacturer’s name, formulation details, batch number and manufacturing/expiry dates, will bear a label with free space for the Investigator sites to enter the following details for each patient:

a) Patient Number

b) Vial number

c) Date of use

This will be provided in **triplicate**– one tear-off label to be stuck on the medication log, one to be stuck on the CRF and the other to remain on the vial.

**Packaging and labeling of AmBisome**

AmBisome for Injection is available as single 50 mg vial cartons and in packs of ten individual vial cartons. Each carton contains one pre-packaged, disposable sterile 5 micron filter.

Each vial of AmBisome, in addition to its original print provided by the manufacturer/ Sponsor bearing the manufacturer’s name, formulation details, batch number and manufacturing/expiry dates, will bear a label with free space for the Investigator sites to enter the following details for each patient:

a) Patient Number

b) Vial number

c) Date of use

This will be provided in **triplicate**– one tear-off label to be stuck on the medication log, one to be stuck on the CRF and the other to remain on the vial.

## Dosing schedule and Administration

### Investigational product (Amphomul^®^)

- Amphomul^®^ shall be administered by IV route at the site of appropriate IV access. It can also be administered into the central venous catheters, if appropriate. The drug should be administered as a slow IV infusion.
- The Investigator or designee will be required to withdraw Amphomul^®^ from the vial(s), and administer each patient the dose specified as slow IV infusion.
- Before administration, Amphomul^®^ will be diluted to 1 mg/mL in 5% dextrose.
- Test dose consisting of 1 mg will be administered in 5% dextrose over a period of approximately 15-20 minutes prior to administration of full-dose infusion of Amphomul^®^.
- The IP (Amphomul^®^)*,* diluted (maximum dilution allowed to 1 mg/mL) in 5% dextrose will be administered as a slow IV infusion over 4 to 6 hours.
- As for use of all Amphotericin B products, facilities for cardiopulmonary resuscitation will be kept readily at hand when administering the drug due to possible occurrence of anaphylactic reactions.
- The patients will be observed for 6 hours following the end of infusion, with appropriate medical treatment readily available in case of a rare anaphylactic reaction during the administration of infusion. Reactions that occur during this time must be recorded by the Investigator in the CRF.
- In case of any toxicity due to study drug, patient will be withdrawn from the study as per investigator’s discretion

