## Patient Completion and Withdrawal

### For each patient, according to the protocol, the study is deemed

- **Completed**

The patient will be administered study treatment as per the protocol, and completes all the safety and efficacy assessments on- Day 7, Day 30, Day 45 (only for patients with splenic aspirate score +1 on Day 30), and at 6 months after study drug administration.

- **Discontinued/withdrawn**- Withdrawal from the study can occur under the following circumstances:
  - 1. Death
    2. Adverse event
    3. Lack of efficacy (treatment failure)
    4. Patient consent withdrawal
    5. Investigator’s discretion
    6. Sponsor’s decision
    7. Pregnancy in a patient
    8. Lost to follow-up*

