### Reference product (AmBisome)

- AmBisome shall be administered by IV route at the site of appropriate IV access. An in-line membrane filter may be used for the IV infusion of AmBisome; provided the mean pore diameter of the filter is not less than 1.0 micron. The drug should be administered as a slow IV infusion.
- The Investigator or designee will be required to withdraw AmBisome from the vial(s), and administer each patient the dose specified as slow IV infusion.
- Before administration AmBisome has to be reconstituted with 12 mL sterile water to yield a preparation containing 4 mg of Amphotericin B/mL. This reconstituted AmBisome will further be diluted with 5% dextrose to a concentration not less than 1 mg/mL.
- Test dose consisting of 1 mg will be administered in 5% dextrose over a period of 10 minutes prior to administration of full-dose infusion of AmBisome.
- AmBisome diluted in 5% dextrose (to a concentration not less than 1 mg/mL) will be administered as a slow IV infusion over 4 to 6 hours.
- As for use of all Amphotericin B products, facilities for cardiopulmonary resuscitation will be kept readily at hand when administering the drug due to possible occurrence of anaphylactic reactions.
- The patients will be observed for 6 hours following the end of infusion, with appropriate medical treatment readily available in case of a rare anaphylactic reaction during the administration of infusion. Reactions that occur during this time must be recorded by the Investigator in the CRF.

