### Duration and Interruption of study drug treatment

In case of any intolerable toxicity or abnormal laboratory findings temporary discontinuation of the study drug as judged necessary by the investigator, will be permitted.

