# 16. CONCURRENT THERAPY

At each study visit, the PI should question the patient/LAR/impartial witness about any medication taken. Concomitant medications are not expected to interfere with study drug administration during the study, unless they lead to clinically significant impairment of the renal function (nephrotoxic drugs such as aminoglycosides).

In case of any IRTs the patient would be administered Tab Acetaminophen 500 mg or Tab Pheniramine 25 mg or injection paracetamol/pheniramine maleate (or any other concomitant medication as per investigator’s discretion) as concomitant medications.

In case of severe hypersensitivity reactions uncontrolled by the above mentioned medications or cardiopulmonary complications of hypersensitivity, the patient would be discontinued from the study and would be treated for the complications appropriately.

Any other concomitant medication administered must also be recorded in the CRF with generic name and/or trade name of the medication, start and end dates of treatment.

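### Only the Amphomul dosing section prompts discretionary withdrawal from the study for any toxicity; in an open-label single-dose trial this invites unequal loss of outcome data, with a bias that could run either way

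*Protocol*

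**What the plan says.** Sections 15.6.1 and 15.6.2 of the protocol list how each product is given. The resuscitation and 6-hour observation items are the same. The Amphomul list then adds a final item: "In case of any toxicity due to study drug, patient will be withdrawn from the study", which the rest of the sentence leaves to the investigator's discretion. No grade is attached to the toxicity. The AmBisome list ends with the observation item, whose last sentence is "Reactions that occur during this time must be recorded by the Investigator in the CRF".

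Other sections deal with the same events without naming an arm:

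- Section 12.6.1: "Withdrawal from the study can occur under the following circumstances", followed by a list that includes adverse event and investigator's discretion.
- Section 15.6.4: "In case of any intolerable toxicity or abnormal laboratory findings temporary discontinuation of the study drug as judged necessary by the investigator, will be permitted". Section 13 (Study Treatment Interruption) has a similar sentence.
- Section 16: "In case of severe hypersensitivity reactions uncontrolled by the above mentioned medications or cardiopulmonary complications of hypersensitivity, the patient would be discontinued from the study". Section 13 (Visit 1, Day 1) has a similar rule.
- Section 12.6.3: a withdrawn patient is asked back once, a week after withdrawal, to record adverse events and be examined. No laboratory tests and no cure assessment are named.

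Section 15.3 states that the trial is open label. Treatment is a single infusion on Day 1.

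**The concern.** The investigator knows the arm, and the instructions for one arm contain an additional reason to take a patient out of the study. The trigger is wide: any toxicity, with no grade. Section 18.3.3 treats all expected reactions as drug related, and Section 9.5 lists chills, fever and vomiting among the more common side effects.

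After a single infusion, leaving the study for toxicity that appears later does not reduce exposure. What it ends is data collection. At stake are the Day 30/45 parasitology and the 6-month definitive cure on which non-inferiority is judged. Day 7 may be at stake too: under the Study Calendar it is the only scheduled post-dose laboratory point in the DLT window. If these losses occur more often in one arm, the comparison is distorted, and outcomes that were never collected cannot be restored by the choice of analysis set.

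**Working it through.** **1. The rules side by side**

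| Section | Event | Consequence | Arm |
|---|---|---|---|
| 15.6.1 | any toxicity | withdrawal from study, at discretion | Amphomul |
| 15.6.2 | reaction during observation | record in CRF | AmBisome |
| 12.6.1 | adverse event, or discretion | withdrawal from study possible | both |
| 13, 15.6.4 | intolerable toxicity or abnormal laboratory findings | temporary stop of drug permitted | both |
| 13, 16 | severe uncontrolled hypersensitivity or cardiopulmonary complications | discontinued from study | both |

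The power to withdraw exists in both arms. The explicit prompt for any toxicity exists in one.

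**2. What withdrawal does to the primary analysis.** Section 17.2 puts the first efficacy assessment at Day 30. MITT needs at least one efficacy assessment and PP needs the study visits (Section 20.1). Non-inferiority is tested in those two sets (Section 20.2.2). A patient withdrawn before Day 30 is therefore likely to be in neither. Section 17.2 also counts treatment discontinuation due to intolerance as failure, and a dose left incomplete because of a DLT as non-evaluable. Neither clearly fits a patient who received the full infusion and was then withdrawn for toxicity.

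**3. The plan's own figures.** Inflation for 20% loss: 400/0.80 = 500; by arm, 300/0.80 = 375 and 100/0.80 = 125. This reproduces the stated numbers. The expected cure rate is not stated. With one-sided alpha 0.025, 80% power, margin 0.10 and 3:1 allocation, the AmBisome number is (1.96 + 0.84)² × p(1−p) × (1 + 1/3) / 0.10². At p = 0.893 this gives 100, hence 400 in total, so 0.893 is used below where power is needed.

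**4. If withdrawn patients are excluded.** Assumptions: true Amphomul cure 0.90; a fraction w withdrawn, with cure rate q; no matching loss under AmBisome. Observed cure = (0.90 − w·q)/(1 − w). Change in points:

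| w | q = 0.5 | q = 0.7 | q = 0.9 |
|---|---|---|---|
| 2% | +0.8 | +0.4 | 0 |
| 5% | +2.1 | +1.1 | 0 |
| 10% | +4.4 | +2.2 | 0 |

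Example: (0.90 − 0.05 × 0.7)/0.95 = 0.9105, which is +1.1 points. Of 375 patients, 2%, 5% and 10% are about 8, 19 and 38. The smaller number alone hardly matters: at cure 0.893, power goes from 80.0% to 79.5% at w = 5%.

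**5. If they are counted as failures, in that arm only.** With cure 0.893 and 300:100 evaluable, the difference shifts by −0.893·w, and power = Φ[(0.10 − 0.893·w)/SE − 1.96].

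| w | Shift (points) | Power |
|---|---|---|
| 0 | 0 | 80% |
| 2% | −1.8 | 62% |
| 5% | −4.5 | 32% |
| 10% | −8.9 | 5% |

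If 5% were counted as failures in both arms, the difference would not shift and power would be 67.5%. The additional fall to 32% comes from the asymmetry.

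**The case against.** Several stronger readings are tempting, and the protocol does not support them.

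- *That Amphomul patients must be withdrawn for toxicity.* The sentence ends by leaving this to the investigator. It is a permission.
- *That only the test arm can lose patients this way.* Section 12.6.1 covers both arms, and the hypersensitivity rules in Sections 13 and 16 name no arm.
- *That Sections 13 and 16 reserve discontinuation for severe hypersensitivity, so that Section 15.6.1 flatly contradicts them.* Neither says only, and Section 12.6.1 shows that they are not exhaustive. Section 15.6.4 concerns pausing the drug; Section 15.6.1 concerns leaving the study. They fit together poorly but do not exclude each other.
- *That Day 7 data will be lost and Amphomul toxicity under-recorded.* Sections 8 and 13 assess every patient for DLT to Day 7 and keep every patient in hospital until then. Sections 18.2.3 and 18.3.5 require re-evaluation within 2 weeks if an adverse event is present at withdrawal, and treated patients stay in the safety set. The toxicity that prompted withdrawal should be on record. Later laboratory worsening is what might be missed.
- *That the bias favours non-inferiority.* This holds only if the patients are excluded and do worse than the rest. Counted as failures, they move the result against Amphomul.

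Section 12.6.2 also asks investigators to try to contact patients who miss follow-up visits, but it does not require the cure assessments.

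What remains is the one-arm prompt. Discretion does not remove it: in an open-label trial, discretion is the route by which unequal withdrawal would arise.

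**Conclusion.** The point stands in limited form. Section 15.6.1 gives a discretionary prompt to withdraw for any toxicity that Section 15.6.2 lacks, in a trial where investigators know the arm and where withdrawal after the infusion mainly ends follow-up. The Day 30/45 and 6-month cure outcomes can be lost; loss of Day 7 laboratory data is possible but not prescribed.

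The size cannot be determined from the protocol. Under the assumptions shown (2% to 10% withdrawn in one arm only), the effect runs from 0 to +4.4 points if patients are excluded and from −1.8 to −8.9 points if they count as failures, against a 10-point margin. It is zero if they are excluded and have the same cure rate as the rest. It would also cancel from the difference if exclusion were equally frequent, with equal cure rates, in both arms. Neither the sign nor the size should be presented as established.

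**What to change.** 1. Use the same toxicity wording in Sections 15.6.1 and 15.6.2.
2. Have the sponsor reconcile Sections 12.6.1, 13 (Visit 1 Day 1, and Study Treatment Interruption), 15.6.1, 15.6.2, 15.6.4 and 16 on when toxicity leads to interruption, to stopping the infusion or to withdrawal. Which clinical rule applies is for the sponsor; this review takes no position on it.
3. Amend Sections 12.6.1 and 12.6.3 to separate stopping or withdrawal from the end of data collection. For example: *A patient in either arm who stops the infusion or is withdrawn because of toxicity still has the scheduled Day 7, Day 30, Day 45 (where applicable) and 6-month assessments, unless consent is withdrawn.* Changing Section 15.6.1 alone would not be enough, because Section 12.6.1 would still allow the same loss in both arms.

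The cost is protocol wording and a few more follow-up visits, all of them already in the Study Calendar. The change should precede enrolment, since missed assessments cannot be recovered later.

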### Reference product (AmBisome)

- AmBisome shall be administered by IV route at the site of appropriate IV access. An in-line membrane filter may be used for the IV infusion of AmBisome; provided the mean pore diameter of the filter is not less than 1.0 micron. The drug should be administered as a slow IV infusion.
- The Investigator or designee will be required to withdraw AmBisome from the vial(s), and administer each patient the dose specified as slow IV infusion.
- Before administration AmBisome has to be reconstituted with 12 mL sterile water to yield a preparation containing 4 mg of Amphotericin B/mL. This reconstituted AmBisome will further be diluted with 5% dextrose to a concentration not less than 1 mg/mL.
- Test dose consisting of 1 mg will be administered in 5% dextrose over a period of 10 minutes prior to administration of full-dose infusion of AmBisome.
- AmBisome diluted in 5% dextrose (to a concentration not less than 1 mg/mL) will be administered as a slow IV infusion over 4 to 6 hours.
- As for use of all Amphotericin B products, facilities for cardiopulmonary resuscitation will be kept readily at hand when administering the drug due to possible occurrence of anaphylactic reactions.
- The patients will be observed for 6 hours following the end of infusion, with appropriate medical treatment readily available in case of a rare anaphylactic reaction during the administration of infusion. Reactions that occur during this time must be recorded by the Investigator in the CRF.

### Premedication

Patients will not be given any premedications prior to infusion of study drugs. However, in case of infusion related events during the infusion of the study drug and if considered necessary by the investigator appropriate concomitant medications will be administered.

### Duration and Interruption of study drug treatment

In case of any intolerable toxicity or abnormal laboratory findings temporary discontinuation of the study drug as judged necessary by the investigator, will be permitted.

## Medication Compliance

Since study drug will be administered by the investigator-team personnel, all patients who complete the study as per protocol will qualify for 100% compliance.

Patients, who do not complete the drug administration schedule as mentioned in the protocol, will be considered non-compliant for the purposes of this study.

# 16. CONCURRENT THERAPY

At each study visit, the PI should question the patient/LAR/impartial witness about any medication taken. Concomitant medications are not expected to interfere with study drug administration during the study, unless they lead to clinically significant impairment of the renal function (nephrotoxic drugs such as aminoglycosides).

In case of any IRTs the patient would be administered Tab Acetaminophen 500 mg or Tab Pheniramine 25 mg or injection paracetamol/pheniramine maleate (or any other concomitant medication as per investigator’s discretion) as concomitant medications.

In case of severe hypersensitivity reactions uncontrolled by the above mentioned medications or cardiopulmonary complications of hypersensitivity, the patient would be discontinued from the study and would be treated for the complications appropriately.

Any other concomitant medication administered must also be recorded in the CRF with generic name and/or trade name of the medication, start and end dates of treatment.

## Concurrent Medication

### Prohibited Medication

1. Any other investigational drugs during the entire study duration
2. Antileishmanial drugs other than study drug during entire study duration.
3. Corticosteroids
4. Skeletal muscle relaxants
5. Cyclosporin
6. Digoxin
7. Vancomycin
8. Aminoglycosides
9. Antifungal
10. Immunosuppresive agents
11. All potentially nephrotoxic drugs should be used with caution.

### Permitted Medications

Medications for other concomitant conditions/diseases

Antibiotics, drugs for restoring cardiorespiratory, metabolic and other systemic functions, premedications, total parenteral nutrition and any blood or platelet transfusion used will be properly documented.

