## ENDPOINTS

### Primary

- Proportion of patients with Amphomul^®^ 15 mg/kg as a single dose infusion achieving
  - Initial cure (splenic aspirate score 0 on Day 30 or on Day 45)
  - Clinical improvement on Day 30 after study drug administration.
    - Absence of fever; and >1 out of following:
      - Increase in hemoglobin concentration by >10% compared to baseline
      - Weight gain compared to baseline
      - Decrease in spleen size by >33% compared to baseline
  - Definitive cure

1. Initial cure at Day 30 or Day 45
2. No signs and symptoms of relapse of Kala-azar for 6 months after study drug administration. If signs and symptoms of relapse of the disease are suspected at any time during the 6 months follow up, splenic aspirate shall be performed at 6 months or earlier after study drug administration.

Proportion of patients achieving all three-efficacy endpoints will be compared across the two groups.

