**DLTs during the study:**

- Recruitment of all subsequent patients in any dosage regimen will be stopped or discontinued if the overall percentage of patients in the study with DLT is >33%. This criterion will only be applicable after randomization of 25^th^ patient in either arm.
- DLT of the study drugs for this study is defined as:

i) Any drug related grade III or higher AE classified as nephrotoxicity/ hepatotoxicity evaluated as per NCI-CTC-AE-v3).

ii) Any other drug related grade IV or higher toxicity except hematological toxicity (evaluated as per NCI-CTC-AE-v3).

iii) If patient’s hematological parameter is in CTC grade III or grade IV at baseline, then a DLT would be considered if there is reduction of ≥33% from baseline.

iv) If patient’s hematological parameter is within normal range or is in CTC grade I or CTC grade II at baseline, then a DLT would be considered if the parameter drops to grade IV or higher

- All the patients will be assessed for DLT up to Day 7 after the administration of first dose of the study drug.

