## Efficacy endpoints

- Proportion of patients with Amphomul^®^ 15 mg/kg as a single dose infusion on Day 1 achieving
  - Initial cure (splenic aspirate score 0 on Day 30 or on Day 45)
  - Clinical improvement on Day 30 after study drug administration
  - Absence of fever; and >1 out of following:
    - Increase in hemoglobin concentration by >10% compared to baseline
    - Any weight gain compared to the baseline visit
    - Decrease in spleen size by >33% from baseline
  - Definitive cure:

1. Initial cure at Day 30 or Day 45
2. No clinical signs and symptoms of relapse of Kala-azar for 6 months after study drug administration. If clinical signs and symptoms of relapse of the disease is suspected at any time during the 6 month follow up, splenic aspirate shall be performed at 6 months or earlier after study drug administration.

Proportion of patients achieving all three-efficacy endpoints will be compared across the two groups.

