### Efficacy Analysis

**Efficacy Endpoints**: Proportion of patients achieving

- Initial cure (splenic aspirate score on Day 30 and 45)
- Clinical improvement on Day 30 after first dose of study drug
  - Absence of fever; and >1 out of following:
    - Increase in hemoglobin concentration by ≥10% compared to baseline
    - Weight gain compared to baseline visit
    - Decrease in spleen size by >33% compared to baseline
- Definitive cure:

1. Initial cure at Day 30 or Day 45
2. No clinical signs and symptoms of relapse of Kala-azar for 6 months after study drug administration. If clinical signs and symptoms of relapse of the disease is suspected at any time during the 6 month follow up, splenic aspirate shall be performed at 6 months or earlier after study drug administration.

Proportion of patients achieving all three-efficacy endpoints will be compared across the two groups.

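### Clinical improvement credits a hemoglobin rise that can come from donor blood, because transfusion is permitted and no scoring rule covers it

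*Protocol*

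**What the plan says.** **Supportive care.** Section 16.1.2 (Permitted Medications) ends: "premedications, total parenteral nutrition and any blood or platelet transfusion used will be properly documented". Neither transfusion nor parenteral nutrition is on the prohibited list in Section 16.1.1. The opening of Section 16 has concomitant medication recorded with start and end dates.

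**Clinical improvement at Day 30.** Section 10.2.1 requires "Absence of fever; and >1 out of following". The items are:
- "Increase in hemoglobin concentration by >10% compared to baseline"; Section 20.2.2 uses ≥10% instead of >10%.
- "Any weight gain compared to the baseline visit" (Section 17.1), or in Section 20.2.2 "Weight gain compared to baseline visit".
- "Decrease in spleen size by >33% from baseline" (Section 17.1).

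The Study Summary repeats the definition. None of these places puts a condition on transfusion.

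**Role of the endpoint.** Section 10.2.1 lists clinical improvement under the primary endpoints and adds: "Proportion of patients achieving all three-efficacy endpoints will be compared across the two groups". In Section 20.2.2, however, the primary efficacy analysis is non-inferiority on definitive cure alone. Clinical improvement is tabulated with a confidence interval under the secondary efficacy analysis.

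**Hematological DLTs (Section 13).** For a parameter at grade III or IV at baseline, "then a DLT would be considered if there is reduction of ≥33% from baseline". For a better baseline, the trigger is a drop to grade IV. Assessment runs to Day 7.

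**Blinding.** Section 15.3 states that neither investigators nor patients are blinded.

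**The concern.** The hemoglobin item is there to show recovery after treatment. A red-cell transfusion raises the same measurement whether or not the drug worked. The protocol admits patients with hemoglobin down to 5 g/dL (Section 12.3), so transfusion during the trial is foreseeable. Yet the rule, applied literally, credits the transfused value to the patient's response.

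Two of the three items suffice, and the weight item has no minimum. Once donor blood supplies the hemoglobin item, a trivial weight gain completes a success. Staff who know the arm decide on transfusion, so its frequency could differ between arms for reasons unrelated to response. What is at stake is whether the clinical-improvement comparison can be interpreted, along with the part it plays in the comparison of all three endpoints.

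**Working it through.** The plan states no figure on this point that could be reproduced. The check is of the scoring rule itself.

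**1. Threshold.** The rise needed is more than 0.10 × baseline hemoglobin:
- baseline 5 g/dL (the entry floor): 0.10 × 5 = 0.5 g/dL
- baseline 8 g/dL: 0.10 × 8 = 0.8 g/dL
- baseline 10 g/dL: 0.10 × 10 = 1.0 g/dL

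Whether a given transfusion exceeds this at Day 30 depends on its volume, its timing and the patient's size. The protocol gives none of these, and entry starts at age 5.

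**2. Scoring patterns.** Three yes/no items give 2³ = 8 patterns among afebrile patients. Four have at least two items met and are successes already. The four failures, and the effect of meeting the hemoglobin item through donor blood, are:

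| Hemoglobin | Weight | Spleen | Scored now | Hemoglobin item met by transfusion |
|---|---|---|---|---|
| no | no | no | failure | failure |
| no | no | yes | failure | success |
| no | yes | no | failure | success, no spleen response |
| yes | no | no | failure | failure |

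Two of the four failure patterns become successes. In a febrile patient no pattern changes, because absence of fever is required separately.

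**3. Reach into the other endpoints.**
- Definitive cure is initial cure (aspirate score 0) followed by no relapse. Hemoglobin and weight do not enter it.
- The sample size in Section 11.2 (300 + 100 evaluable, margin -0.10) also rests on definitive cure.
- If the all-three comparison is read as joint success, it also needs parasitological cure. Donor blood can decide it only in a patient who already has both cures.

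**4. Size, for orientation only.** Let *e* be the excess proportion transfused in one arm, and *f* the share of transfused patients whose failure is turned into a success, taken as equal in both arms. The difference in clinical improvement then shifts by *e* × *f*. Both inputs are assumptions:
- *e* = 0.05, *f* = 0.10: 0.05 × 0.10 = 0.005, or 0.5 percentage points
- *e* = 0.20, *f* = 0.30: 0.20 × 0.30 = 0.06, or 6 percentage points

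The documents support no particular value in this range, nor its direction.

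**5. DLT window.** After dosing, the only fixed safety laboratory up to Day 7 is on Day 7 (Study Calendar). Day 1 tests are discretionary. A transfusion of the relevant component before the Day 7 count could therefore keep a fall from being seen. A qualifying value already measured remains a DLT.

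**The case against.** The strongest case is that the trial's conclusion does not depend on this. The only decision rule is on definitive cure, and clinical improvement is formally secondary. How concomitant treatment enters the derivation of a secondary endpoint is often left to the SAP, and the data needed are already collected. The first part stands and limits the weight of the point. The second stands only in part. The protocol fixes the scoring rule itself and repeats it in four places, and followed as written that rule counts donor blood as improvement.

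It is also fair that scoring a transfused patient as not met is a penalty that can bias the other way. A sensitivity analysis should therefore accompany it.

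A reader might infer several stronger things that the documents do not support:
- **That parenteral nutrition manufactures the weight item.** Nothing indicates how often it would be used. Weight is judged at Day 30, 30 − 7 = 23 days after the planned discharge. This is speculative, and reporting its use by arm is enough.
- **That transfusion can erase a DLT.** It cannot undo a value already recorded. Only masking before a measurement is possible, and nothing shows that masked cases would change the >33% recruitment stop.
- **That DLTs should be scored on pre-transfusion values only.** That would discard a later fall to grade IV after transfusion, which the present text counts.

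**Conclusion.** The point holds for the hemoglobin item of clinical improvement. With transfusion permitted and no scoring condition, an afebrile transfused patient can be counted as clinically improved through donor blood plus any weight gain. Two of the four afebrile failure patterns can be turned into successes this way.

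Bias between arms follows only if transfusion or its effect on scoring differs by arm. Open-label treatment makes that possible but does not establish it. It would be going too far to say that the bias favours the worse arm, or to state how many patients are affected: the protocol gives no transfusion rate, and the 0.5 to 6 point range rests wholly on assumed inputs. The non-inferiority test on definitive cure and the sample size are untouched. The correction is worth making because it is cheap and the endpoint is listed as primary in Section 10.2.1, but the validity of the main conclusion does not hang on it.

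**What to change.** - **Endpoint definition.** In Sections 10.2.1, 17.1 and 20.2.2, and in the Study Summary where the definition is repeated, state that the hemoglobin item is scored as not met if a red-cell transfusion was given between baseline and the Day 30 sample. The patient can still qualify on weight and spleen. The same edit can align >10% with ≥10%.
- **Sensitivity analysis.** Repeat the analysis with the item scored as measured. If transfusion does not lower the Day 30 value, the two scorings bracket each arm's proportion.
- **Reporting.** Tabulate transfusion and parenteral nutrition by arm.
- **DLTs.** Leave the definition as it is, with every value up to Day 7 counting. In the DLT report, flag patients transfused with the relevant component before their Day 7 count, since a fall may have been masked.

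The cost is one sentence in the endpoint definition, one extra analysis and two descriptive outputs, all from data already recorded. The downside is that a transfused patient who truly improved must qualify on the other two items. Nothing changes about who may be transfused or fed.
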